**Figure 2 F2:**
[figure not shown]
Trial flowchart from randomisation to completion at 12 month follow-up.

### The interventions

The intervention arm practice nurses undertake a two-day training in facilitation skills associated with use of the Diabetes Manual, including practical skill development and underlying theoretical principles of self-efficacy [see Additional file 1]. The nurse training syllabus incorporates efficacy enhancing mechanisms and therefore provides an experiential model for the nurses. Recruited patients have a 20 minute consultation with the trained nurse to introduce the 12-week Diabetes Manual programme. The first two patients that each nurse delivers the intervention to are intended to be practise consultations with ineligible patients to ensure she has gained familiarity with the intervention delivery procedures. The control arm receives usual care for a period of six months. Following six-month data collection, control arm nurses receive the training and deliver the Diabetes Manual to the recruited patients in their practice. No further trial data is collected from control arm participants thereafter.

### Trial management

A trial steering group has been formed consisting of the full research team, the nurse trainer, a practice nurse and two lay people from the Warwick Diabetes Care Research User Group. Due to the low risk nature of the interventions, a data monitoring committee is not necessary.

### Quality assurance

Standardised delivery of the interventions will be assured by i) the nurse training programme being accompanied by detailed written material to which the nurses can refer during the intervention delivery; ii) analysis of a telephone support data sheet used by the nurses to prompt and record telephone discussion; iii) the nurse audio records 1 in 6 telephone support calls and the teaching and research team listen to half of these calls, and assesses them against the training protocol for telephone support and iv) 12 patients in each arm will be invited to participate in a semi-structured interview, and this data will be analysed to provide evidence of protocol adherence by the nurses for a selection of the patients and programme adherence by the patients.

### Qualitative Study

#### Patient interviews

Twelve semi-structured interviews are being undertaken with a purposive sample from each arm of the trial (n = 24). Sampling aims to capture differing self-efficacy levels and educational attainment and practice location. The interviews will explore any differences in the intervention and control arm experience of diabetes management during the trial period. The interviews are completed during a two-week period following completion of the six-month questionnaire data and before the collection of follow-up clinical data so that the interview does not influence the questionnaire completion. The interviews' close proximity to the clinical follow-up review will limit its influence on clinical outcomes such as HbA1c.

#### Health professionals' views

Two focus groups will be held following six-month data collection for trained, intervention arm, practice nurses to capture their perspective of the Diabetes Manual programme.

### Sample size and rate of recruitment

We originally sought power of 90% (alpha = 0.05) to detect a 0.6% difference in individual patient HbA1c between intervention and control arms. Based on feasibility work, we estimated that the number of patients who have type 2 diabetes per recruited practice that meet the inclusion criteria would be an average of 80 so it would be reasonable for each practice to recruit and manage between 5–12 patients (expected mean number of patients = 10). Using an intra cluster correlation for HbA1c of 0.043 and allowing for 15% patient attrition and variability in clusters size gives an adjusted sample size of 212 in each arm. Allowing for an attrition rate of 10% for practices, we aimed to recruit a total of 46 practices, each willing to recruit up to12 patients. Because of the lower rate of patient recruitment in the first twelve months, we expected fewer patients per practice. We compensated for this by recruiting more practices. We estimated that with analysable data on five patients per practice in 50 practices the power of our study to detect a 0.6% difference would be 80% (accounting for between cluster correlation and variable cluster size as described above). This gives a lower power than we originally aimed for but was a realistic target.

### Statistical analysis

Data is double entered and discrepancy checks carried out with source data. To account for clustering by practice, primary and secondary outcomes will be analysed using population averaged models with robust standard errors (using generalised estimating equations). Patient and practice level covariates thought to be related to outcome, including practice self-assessed quality of diabetes care indicators [28], geographical location of practice, level of patient outcome at baseline (where available), and patient age, gender, education and socio-economic status will be considered for incorporation in the analysis. Covariates will be included if they show a strong (α<10%) relationship with outcome. We will also include a covariate representing whether the practice was recruited before or after the change in protocol relating to HbA1c levels. To detect the presence of any significant differences in effect between sub-groups, we will fit first order interaction terms for interactions between intervention and the following factors which represent the sub-groups of interest: laboratory used for blood sample analysis, patient age and educational attainment. Separate models will also be fitted for the separate subgroups, but these results will be exploratory rather than definitive. The questions we aim to explore in the subgroup analyses are: Is the effect on HbA1c different for patients recruited before and after the protocol change or for patients in different age groups? Is any effect on self-efficacy different for older and younger patients or by educational attainment?

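### GEE with robust standard errors on about 50 small practices: unless a small-sample correction is specified, the two-sided type I error is about 6-8% rather than 5%

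*Protocol article*

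**What the plan says.** The Statistical analysis section of the protocol article fixes one method for all outcomes: "primary and secondary outcomes will be analysed using population averaged models with robust standard errors (using generalised estimating equations"). It does not say which robust variance is meant, or whether tests use a normal or a t reference.

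The same section sorts the practice-level covariates into two kinds. A term for recruitment before or after the HbA1c protocol change is always included. Practice quality indicators and practice location are only candidates; they enter if related to outcome at the 10% level. The section also plans interaction tests for subgroups and adds that "Separate models will also be fitted for the separate subgroups", calling those results exploratory.

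The Sample size and rate of recruitment section gives the number of clusters. The original plan was stated as "We originally sought power of 90% (alpha = 0.05) to detect a 0.6% difference in individual patient HbA1c" and led to 46 practices. The revised calculation is made "with analysable data on five patients per practice in 50 practices", for 80% power. The inputs are introduced by "Using an intra cluster correlation for HbA1c of 0.043 and allowing for 15% patient attrition and variability in clusters size".

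**The concern.** The sandwich variance behind robust GEE standard errors is justified as the number of clusters becomes large. With about 50 clusters it tends to be too small, because it is built from fitted residuals, which are smaller than the true errors. It is also itself variable, which a normal reference ignores.

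Three features of this design make the problem worse. Treatment is assigned to practices, so the treatment contrast lies entirely between practices. Practice sizes vary. And at least one further practice-level term is always in the model, which uses up between-practice information.

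At stake is whether the primary HbA1c comparison holds the stated alpha of 0.05, and whether its confidence interval has the coverage claimed for it. The same method is applied to every secondary outcome.

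**Working it through.** **Inputs from the protocol article.** Alpha 0.05 (sidedness not stated; two-sided taken); difference 0.6% HbA1c; intracluster correlation 0.043; 212 patients per arm originally, with 15% patient attrition and an expected mean of 10 patients per practice; revised design 50 practices with 5 analysable patients each; at most 12 patients per practice; minimisation on mean HbA1c, quality indicators and number recruited; the 10% covariate rule; the protocol-period term always included.

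**Assumed, because the article does not give them.** The SD of HbA1c; the variation in practice size; a baseline-outcome correlation of 0.5; three location categories; 60% of practices recruited before the protocol change; candidate covariates without a true effect on outcome.

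**Step 1: reproduce the plan's own power.**
- Original design: 10 × 0.85 = 8.5 analysed patients per practice; design effect 1 + (8.5 − 1) × 0.043 = 1.3225; analysed per arm 212 × 0.85 = 180.2; effective size 180.2 / 1.3225 = 136.3.
- Setting 136.3 = 2 × (1.960 + 1.282)² × SD² / 0.6² gives SD ≈ 1.53.
- Revised design: design effect 1 + (5 − 1) × 0.043 = 1.172; effective size per arm 125 / 1.172 = 106.7; standard error 1.53 × √(2 / 106.7) ≈ 0.21; power Φ(0.6 / 0.2095 − 1.96) ≈ 0.82.

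This is within 2 points of the stated 80%. Other readings of the attrition and cluster-size allowances give 0.75-0.88. The revised sample size is therefore reproduced, and the design it describes is the right one to simulate.

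**Step 2: simulate the analysis with no treatment effect.** Exchangeable GEE, 50 practices of mean size 5, baseline HbA1c in the model, practices minimised. Two size patterns were used: strongly unequal (1-12, coefficient of variation about 0.6) and moderately unequal (2-8, coefficient of variation 2/5 = 0.4). The Monte Carlo standard error is about 0.4-0.6 points.

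| Model (50 practices) | Null trials | Uncorrected sandwich, normal reference | Kauermann-Carroll, t | Mancl-DeRouen, t | Mean estimated SE / true SE |
|---|---|---|---|---|---|
| Baseline and period; sizes 1-12 | 4000 | 7.3% | 5.6% | 4.7% | 0.936 |
| Plus candidates passing the 10% rule; sizes 1-12 | 2500 | 7.6% | 5.7% | 4.6% | 0.934 |
| Plus candidates passing the 10% rule; sizes 2-8 | 2000 | 6.3% | 4.6% | 3.9% | 0.953 |
| All candidates forced in (4 practice-level terms); sizes 1-12 | 4000 | 9.4% | 5.8% | 3.9% | 0.888 |

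Under the 10% rule an average of about 1.6 practice-level covariates entered, counting the period term. A further run of the baseline-and-period model (1500 null trials per setting) gave 6.7-7.7% uncorrected and 4.1-4.7% with Mancl-DeRouen and t. With no covariates at all, and practices randomised without minimisation, the uncorrected error was 5.8% (equal sizes) and 6.2% (unequal sizes).

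**Step 3: check that the mechanism explains the size.** A standard error at 0.936 of its true value turns the critical value 1.96 into 1.96 × 0.936 = 1.835, and the two-sided normal probability beyond 1.835 is 6.7%. Separately, with 50 − 2 − 1 = 47 degrees of freedom, the probability that |t| exceeds 1.96 is 5.6%. The downward bias and the missing t reference together account for the simulated 7.3%. Multiplying the variance by K/(K − 1), a common software scaling, lowers the error by only about 0.1-0.4 points.

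**The case against.** The strongest objection is that the defect is inferred. The article says robust and does not say uncorrected; the choice of sandwich variant and reference distribution is often left to a statistical analysis plan, which is not shown. GEE is a suitable model for a cluster trial. This stands as far as it goes, and it makes the point conditional. It does not remove the point: the article names the variance method, and that method as usually implemented does not hold the stated alpha in this design.

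Three stronger readings are tempting, and the article does not support them.

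- *Only about 45 practices will be analysed.* A reader might infer this from "Allowing for an attrition rate of 10% for practices". That allowance belongs to the original calculation, in which "we aimed to recruit a total of 46 practices". The revised figure of 50 is already described as practices with analysable data, so taking 10% off it counts the loss twice. The inflation is present at 50.
- *The error is 10% because several practice-level covariates are in the model.* Only the period term is certain. Quality indicators and location must pass the 10% rule, and with that rule applied the error stays at about 6-8%.
- *The separate subgroup models rest on far fewer practices.* Age and education vary between patients within a practice, so most practices contribute to each subgroup. Only splits that follow the practice, such as before or after the protocol change, divide the practices. The article already calls the separate models exploratory, so no error rate is claimed for them here.

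The practice sizes are also assumed. The article gives a cap of 12 and an original range of 5-12, but no coefficient of variation. With sizes 2-8 the error is 6.3%, so the lower end of the range is as plausible as the upper.

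**Conclusion.** The point holds in conditional form. If the uncorrected sandwich is used with a normal reference, the primary test runs at about 6-8% two-sided instead of 5%. The estimated standard error is on average about 0.93-0.95 of its true value, so the interval is about 5-7% too narrow before allowing for the t reference. About 9-10% is reached only when nearly all candidate practice-level covariates are retained. These figures rest on the plan's 50 practices, mean size 5 and intracluster correlation of 0.043, and on the assumed size variation, baseline correlation, location categories and period split. The inflation is modest, but it affects the primary test and is cheap to prevent.

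**What to change.** State the variance estimator and the reference distribution in the analysis section or in the statistical analysis plan. Either of these would do:

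- GEE with a bias-corrected sandwich (Kauermann-Carroll or Mancl-DeRouen) and a t reference with degrees of freedom equal to the number of practices minus the number of practice-level parameters. With intercept, treatment and period only, that is 50 − 3 = 47.
- For continuous outcomes, a linear mixed model with a practice random effect and Kenward-Roger degrees of freedom.

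Apply the choice to the primary and secondary models, and to exploratory models that split the trial by practice, such as before or after the protocol change. If an analysis plan outside the article already specifies this, a cross-reference is enough.

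The cost is a sentence and a software option, slightly wider intervals, and slight conservatism with Mancl-DeRouen (3.9-4.7% in the 50-practice settings tabulated above). Kauermann-Carroll stays closer to nominal, at 4.6-5.8%.

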### Baseline assessment

Baseline clinical assessment was conducted by the practice nurse prior to randomisation during an additional diabetes review. Blood samples for HbA1c assessment, total and HDL cholesterol were taken by the nurse and analysed outside the practice by the DCCT aligned [27] laboratory blinded to practice or patient group allocation. A self-completion booklet of questionnaires consisting of demographic questions, the problem areas in diabetes scale (PAID) [29], the diabetes management self-efficacy scale (DMSES) [30] and the diabetes self-care activities measure [31] was given to the patient by the nurse at baseline for return in replied paid envelope to the research team. Process data consisted of the diabetes self-care activities scale [31] and prescribed medication collected by the practice nurse during clinical assessment. Demographic data includes age, gender, net weekly income, highest educational qualification, ethnicity and duration of diabetes.

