### Group allocation

Following patient baseline data collection, practices were minimised [32] into intervention and control arms according to mean HbA1c of recruited patients, practice self-assessed quality of diabetes care indicators [28] and the number of individuals recruited [figure 2]. Computer-aided minimisation was undertaken by a statistician blind to practice identity. All members of the research team who will be inputting, analysing and interpreting both qualitative and quantitative data are blind to the group allocation of practices and participants. The nurse trainer, one research fellow and one secretary remain unblinded to ensure effective communication and support between the research team, the practices and the participants regarding training events and follow-up data collection.

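### The primary HbA1c model takes its covariates from a 10% test against the observed outcome, so baseline HbA1c and the allocation factors are not fixed in advance

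*Protocol article*

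**What the plan says.** The Statistical analysis section of the protocol article plans population-averaged models (GEE with robust standard errors) for primary and secondary outcomes. It lists candidate covariates at practice and patient level: quality-of-care indicators, practice location, and then "level of patient outcome at baseline (where available), and patient age, gender, education and socio-economic status will be considered for incorporation in the analysis". The list is introduced as an inclusion, so it is not closed. The entry rule is "Covariates will be included if they show a strong (α<10%) relationship with outcome". One covariate is exempt: "We will also include a covariate representing whether the practice was recruited before or after the change in protocol relating to HbA1c levels".

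Two other sections bear on this. Under Group allocation, "practices were minimised [32] into intervention and control arms according to mean HbA1c of recruited patients", together with the quality indicators and the number of patients recruited. Under Baseline assessment, "Baseline clinical assessment was conducted by the practice nurse prior to randomisation during an additional diabetes review", and the blood sample for HbA1c was part of it. Group allocation also states: "All members of the research team who will be inputting, analysing and interpreting both qualitative and quantitative data are blind to the group allocation".

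**The concern.** A confirmatory model should be settled before outcomes are seen. Here, which covariates adjust the treatment effect depends on how they happen to correlate with six-month HbA1c in this sample, and the final standard error takes no account of that step. Baseline HbA1c is measured before randomisation and its practice mean drives the allocation, so nothing prevents it from being fixed, yet formally it must pass a test. The same holds for the quality indicators. The other two minimisation factors are not named at all, although an analysis should reflect the way practices were allocated. Because the rule covers every outcome, HbA1c, cholesterol, blood pressure, BMI and the questionnaire scores could each be adjusted for a different set.

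At stake is whether the primary estimate is defined in advance, and possibly its error rate and precision.

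**Working it through.** **1. Status of each covariate, from the two sections side by side**

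| Covariate | Minimisation factor? | Place in the model |
|---|---|---|
| Eligibility-change indicator | no | always included |
| Baseline value of the outcome | individual value, no | only if it passes 10% |
| Quality indicators | yes | only if they pass 10% |
| Practice mean HbA1c | yes | not named |
| Number recruited | yes | not named |
| Location, age, gender, education, socio-economic status | no | only if they pass 10% |

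**2. The plan's own figure.** Sample size and rate of recruitment states 80% power for a 0.6% difference with five analysable patients in each of 50 practices, ICC 0.043. The SD and the variation in cluster size are not given, so a strict check is impossible. The design effect is 1 + ((CV² + 1)m − 1) × ICC. Back-solving the SD from 212 per arm at 90% power (two-sided 5% assumed; m = 8.5 or 10; CV 0 to 0.5; 15% attrition applied as 212 × 0.85 or 212/1.15) gives 1.44 to 1.55, and then 81% to 85% power at 50 × 5. That is near the stated 80%. The point does not depend on it.

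**3. Chance that a covariate passes the screen.** With equal clusters of five, the design effect is 1 + 4 × 0.043 = 1.172, and the effective n is 250/1.172 = 213.3. By Fisher's z, P(pass) ≈ Φ(atanh(ρ) × √(213.3 − 3) − 1.645), and √210.3 = 14.50.

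- ρ = 0.10: Φ(0.1003 × 14.50 − 1.645) = Φ(−0.19) = 42%
- ρ = 0.15: Φ(0.1511 × 14.50 − 1.645) = Φ(0.55) = 71%
- ρ = 0.20: 90%
- ρ = 0.30: 99.8%

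The threshold corresponds to an observed correlation of tanh(1.645/14.50) = 0.11, or about 1.3% of variance (0.113² = 0.0128). That is not a strong relationship in any usual sense.

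**4. What the uncertain covariates are worth.** Adjusting for a covariate with correlation ρ multiplies the standard error by √(1 − ρ²): 0.995 at ρ = 0.10 and 0.989 at 0.15. The covariates whose entry is a matter of chance therefore change precision by about 1% or less.

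**5. Type I error, same standard-error method on both sides.** Simulated null trials with ICC 0.043; covariate correlations are assumed throughout.

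| Setting | Fixed, baseline only | All candidates fixed | Screened |
|---|---|---|---|
| 50 × 5, cluster-robust SE with t reference, baseline ρ 0.3 (5,000 trials) | 5.1% | 5.6% | 5.1% (arm not in screen), 5.8% (arm in screen) |
| Same, baseline ρ 0.5 | 5.4% | 5.9% | 5.5%, 6.1% |
| 50 × 5, uncorrected robust SE, baseline ρ 0.5 | 6.6% | 7.5% | 7.3% |
| Same, small-sample correction | 5.1% | – | 5.2% |
| 50 × 5, uncorrected, another simulation (1,200 trials) | 6.2% | 7.9% | 6.9–7.2% |

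Monte Carlo error is about 0.3 points with 5,000 trials and 0.7 with 1,200. At the planned size, screening adds 0 to 1.0 points over the fixed baseline model. In a smaller trial than planned (45 practices, mean 4.25 patients, uncorrected SE, 1,200 trials) it was 8.2–9.1% against 7.2%, while fixing every candidate gave 9.2%.

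**6. Baseline HbA1c under the rule.** It was selected in at least 99.8% of the 50 × 5 simulated trials at ρ = 0.3 and in all at ρ = 0.5. With a true difference of 0.6 (SD 1.5, ρ = 0.5, 1,500 trials), power was 80% unadjusted, 89% with baseline fixed, and 89–91% screened.

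**The case against.** The strongest defence is that the rule does little damage. The candidates are named and thought to be prognostic, the threshold is stated, and the analysts are blind to allocation, so the model can hardly be steered towards a favourable effect. Baseline HbA1c would be selected almost without fail. An irrelevant covariate that slips in does not bias a randomised comparison. All of this stands as to size. It does not make the model pre-specified: blinding limits outcome-driven choice but does not remove it. Nor can the matter be left to a statistical analysis plan that is not shown, because the protocol itself states the rule. How the screen is run (one covariate at a time or jointly, with or without arm) may well be set out there, and its absence is not counted here.

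Three stronger readings are tempting and not supported.

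- **The screen pushes type I error well above 5%.** Setting a screened model with uncorrected robust errors (7.3%) against a fixed model with a small-sample correction (5.1%) suggests this, but two things change at once. Like for like it is 7.3% against 6.6%, or 5.2% against 5.1%. Most of the gap comes from the uncorrected variance estimator, which is a separate matter.
- **The plan forfeits the precision from baseline adjustment.** At an assumed correlation of 0.5 the standard error falls by 1 − √0.75 = 13%. Whenever baseline is strong enough to give that, the rule includes it.
- **The open choice takes the error to 9–10%.** Taking the most favourable of five specifications (unadjusted, baseline only, all fixed, two forms of screening) gave 8.7–10.2%. The protocol does not allow that freedom: it states a threshold and blinds the analysts.

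**Conclusion.** The point holds as a defect of pre-specification. The set of covariates in the primary HbA1c model depends on observed outcomes. Baseline HbA1c and one minimisation factor are formally conditional, and two minimisation factors are not named, although individual baseline HbA1c would carry much of the practice mean. Covariates with true correlations of 0.10 to 0.15 are kept in about 42% to 71% of trials, and models may differ between outcomes.

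The consequence is modest: about one point or less of type I error at the planned 50 × 5, and no visible loss of power. This assumes the rule is applied mechanically by blinded analysts, equal clusters of five, ICC 0.043 from the protocol, and the assumed covariate correlations; the protocol gives no correlations and no SD. The rule should be changed, but it does not invalidate the primary analysis.

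**What to change.** Delete the 10% rule for the primary analysis. State the primary model now, before unblinding: arm, baseline value of the outcome, the three minimisation factors (practice mean HbA1c, quality indicators, number recruited), and the eligibility-change indicator that is already planned. Use the same structure for each secondary outcome, with its own baseline value where one exists. Put age, gender, education, socio-economic status and practice location together in one pre-listed sensitivity model, whatever their significance.

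The cost is a change of wording and a few degrees of freedom for covariates that may turn out not to be prognostic. With about 50 practices, the practice-level terms are best entered sparingly, for example as single linear terms.

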### Practices and participants

GP practices from three Strategic Health Authorities in central England have been recruited. Practice eligibility is i) employment of a practice nurse who has undertaken post-registration diabetes care training and ii) use of a laboratory in which HbA1c ranges and assays are DCCT aligned [27] determined and stable. Patient eligibility criteria are adults with type 2 diabetes, not taking insulin and able to read and write English. During the first 12 months of the study, eligible patients had a most recent HbA1c over 8%. We experienced low recruitment over this period as trial commencement concurred with the implementation of a payment linked quality improvement policy [28] during which time GPs have become more aggressive in the prescribing of oral hypoglycemic agents and insulin in an attempt to reduce each patient's HbA1c to below the maximum payment threshold of 7.4%. This has resulted in considerably fewer patients than anticipated meeting the eligibility criteria. It also means that eligible patients include a greater proportion of those for whom more aggressive pharmacological management was not working either due to poor attendance at reviews, complex diabetes management situations or treatment concordance issues. One year into the trial a protocol change was agreed by the investigators, funders and the research ethical committee to enhance patient recruitment by reducing the patient eligibility to a minimum of HbA1c 7%.

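### The robust GEE test of intervention-by-laboratory interaction rests on few practices per cell and over-rejects, mildly with 2–3 equal laboratories and seriously from 4–5 upward

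*Protocol article*

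**What the plan says.** The Statistical analysis section of the protocol article states that "primary and secondary outcomes will be analysed using population averaged models with robust standard errors (using generalised estimating equations"). In that framework it fits first-order interactions of intervention with "laboratory used for blood sample analysis, patient age and educational attainment", with the aim of detecting significant subgroup differences. It then adds: "Separate models will also be fitted for the separate subgroups, but these results will be exploratory rather than definitive".

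Three other sections bear on the laboratory term:

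- Practices and participants makes "use of a laboratory in which HbA1c ranges and assays are DCCT aligned" a condition of practice eligibility. Laboratory is therefore an attribute of the practice.
- Group allocation minimises on mean HbA1c, quality-of-care indicators and number recruited. Laboratory is not a factor, so nothing keeps it balanced between arms.
- Sample size and rate of recruitment gives the revised target: "with analysable data on five patients per practice in 50 practices the power of our study to detect a 0.6% difference would be 80" per cent.

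The article does not give the number of laboratories. It says only that practices come from three Strategic Health Authorities.

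**The concern.** A sandwich variance learns about sampling error from the spread between clusters. For age or education, every practice contributes to both sides of the contrast, so the test draws on all 50 or so practices. For laboratory, each contrast draws only on the practices in the laboratory-by-arm cells concerned. When those are few, the estimated variance is too small on average and too unstable for a chi-square reference. The result is excess false positives, not merely low power.

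At stake is a spurious report that the programme's effect on HbA1c, the primary outcome, depends on which laboratory measured it. Such a report would cast doubt on a sound main result.

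**Working it through.** **Inputs from the article.** 50 practices (25 per arm) with five analysable patients each. The original calculation is described as "Using an intra cluster correlation for HbA1c of 0.043 and allowing for 15% patient attrition and variability in clusters size", which gives 212 per arm with "expected mean number of patients = 10" per practice. The target was: "We originally sought power of 90% (alpha = 0.05) to detect a 0.6% difference in individual patient HbA1c".

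**Inputs assumed.** Two to ten laboratories; one laboratory per practice; uncorrected sandwich variance; two-sided tests. The SD of HbA1c is not given, but a false-positive rate does not depend on it.

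**1. The plan's own figure.** The article gives no error rate for the interaction tests, so the figure to reproduce is the 80% power.

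- Original design effect: 1 + (10 − 1) × 0.043 = 1.387.
- Effective number per arm: 212 × 0.85 / 1.387 = 129.9.
- Implied SD for 90% power: 0.6 / [(1.960 + 1.282) × √(2/129.9)] = 1.49.
- Revised design effect: 1 + (5 − 1) × 0.043 = 1.172, so the effective number per arm is 125 / 1.172 = 106.7.
- Revised power at SD 1.49: about 84%.

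Other readings of attrition and cluster-size variation give 73–86%. The stated 80% lies inside that range, so the design inputs are coherent.

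**2. Practices per cell.** With L equal laboratories, a cell holds n = 50/(2L) practices. With equal practice sizes, the uncorrected sandwich variance of a cell mean averages (n − 1)/n of the truth. For L = 5, n = 5 and the ratio is 0.80. That bias alone moves the 4-df critical value from 9.488 to an effective 0.80 × 9.488 = 7.59. The tail area for 4 df is exp(−x/2)(1 + x/2), which gives exp(−3.795) × 4.795 = 0.108. So the error rate doubles before the instability of the variance estimate (4 df per cell) is counted.

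**3. Simulation under no interaction.** 3,000 runs per row; ICC 0.043; at least one practice in every cell; exchangeable GEE; joint test with L − 1 df at nominal 5%. The Monte Carlo standard error at 5% is √(0.05 × 0.95 / 3000) = 0.4 points.

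| Equal laboratories | Practices per cell | Robust Wald, chi-square | Robust Wald, F reference | Runs with a one-practice cell |
|---|---|---|---|---|
| 2 | 12.5 | 6.8% | 6.2% | 0% |
| 3 | 8.3 | 9.7% | 8.3% | 0% |
| 4 | 6.3 | 15.4% | 13.3% | 1% |
| 5 | 5.0 | 24.8% | 21.0% | 4% |
| 6 | 4.2 | 37.6% | 32.4% | 19% |
| 8 | 3.1 | 69.6% | 63.2% | 71% |
| 10 | 2.5 | 88.8% | 84.3% | 96% |

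A repeat for 2, 3, 4, 5, 6 and 8 laboratories gave about 7%, 9%, 15%, 24%, 38% and 68%. An F reference alone does not repair the test.

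**4. Departures from the equal case (chi-square reference).**

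- Variable practice sizes: 11.8%, 29.2% and 43.3% for 3, 5 and 6 laboratories.
- Unequal laboratories: about 16–30% for 3 and 50% or more for 5, depending on the assumed skew.
- Empty cells: with 8 laboratories, 12–15% of unrestricted allocations left a term that could not be estimated.

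**5. The other tests on the same 50 practices (4,000 runs).** Age interaction 7.0%; education 7.5% (three levels) to 8.5% (four levels); main intervention effect about 6–7%.

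**6. Tests that hold their level.** A practice-level weighted F test with (L − 1, 50 − 2L) df, for example (4, 40) for five laboratories, stays at 4–6%. The Mancl-DeRouen corrected sandwich with an F reference gives 4.2%, 4.6%, 4.6%, 5.5% and 6.3% for 2 to 6 equal laboratories. It cannot be computed when a cell holds a single practice, which happens in most runs with 8–10 laboratories.

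**The case against.** The strongest reply is that the article fixes less than the simulation assumes. It does not rule out a small-sample correction, an F reference or pooling of sparse laboratories, and such details are commonly left to an analysis plan. That is fair, and their absence is not the point here. What stands is that the estimator as stated, used in its standard form, gives wrong error bars for this one factor. Nor can any correction supply practices to an empty cell.

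A reader might infer four stronger things that the document does not support.

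- **That the plan is bound to give a badly inflated error rate.** The laboratory count is unknown, and with 2 or 3 equal laboratories the excess is modest.
- **That the interaction tests are presented as confirmatory.** Read literally, the exploratory label attaches only to the separate models. The sentence that follows, however, introduces the subgroup questions as matters to explore, so this is unclear wording rather than a claim.
- **That a non-significant age or education interaction will be taken as no difference.** The article nowhere says so. Limited power for interactions is ordinary in a trial sized for a main effect.
- **That the laboratory check should go.** None of the listed subgroup questions mentions laboratory, but HbA1c is the primary outcome and is measured in the practices' own laboratories. A consistency check has an evident purpose.

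**Conclusion.** The point holds in conditional form. The standard robust Wald test of intervention by laboratory does not keep its 5% level on about 50 practices. The excess is small at 2–3 equal laboratories (about 7–10%), serious at 4–5 (15–25%) and disqualifying at 6 or more (38% upward). Uneven laboratories bring the serious range down to three. These figures assume five patients per practice unless stated otherwise, ICC 0.043, one laboratory per practice and no small-sample correction. The problem is specific to laboratory: the age and education interactions and the primary comparison are only mildly inflated, and the primary conclusion is not threatened.

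**What to change.** - Count the laboratories and the practices per laboratory in each arm. Pool laboratories that have too few practices per arm, by a rule set before outcomes are compared.
- Test laboratory heterogeneity with a practice-level weighted F test or a permutation test. A small-sample-corrected sandwich variance with an F reference would also do where every cell holds more than one practice.
- Do not fit separate models for sparse laboratories.
- State that all interaction tests, not only the separate models, are exploratory and will be reported as estimates with 95% confidence intervals.

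This changes analysis wording only, with no new data and no change to the primary analysis. The cost is slightly more analysis work and a laboratory test that is less sensitive than the uncorrected one appears to be.
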